### Data entry and coding

Trained secondary coders will undertake independent double data entry of encounter forms into the study’s purpose built database. Encounter data will be coded using the International Classification of Primary Care (ICPC-2), adopted by the World Health Organization as a classification system for primary care [61, 62], and for the chiropractic data ICPC-2 PLUS CHIRO [63]. A quality assurance protocol to ensure reliability of data entry, including the development of computer-aided error checks (‘locks’) at the data entry stage, will be built into the database. Further range and logical data checks will be conducted within the database.

### Data access plan

ICES, funded by the Ontario Ministry of Health and Long Term Care, links encoded population-based health information at the patient level. The practice-level and patient questionnaire data collected by the study team will be migrated to ICES for linkage. Analysis will be conducted using the following ICES datasets: OHIP database for imaging fee codes; OHIP Claims Database; National Ambulatory Care Reporting System Database for emergency room visits; Canadian Institute for Health Information Database for hospitalisation and surgery; Ontario Cancer Registry.

### Sample size justification

The study will be adequately powered to determine factors associated with imaging behaviour, including both clinician (e.g. profession) and patient (e.g. severity and duration of pain) characteristics. We will compare inappropriate imaging rates among professions, assuming base imaging rates across the professions range from 10 to 45% [9, 11, 34, 64, 65]. Using an intracluster correlation coefficient estimate of 0.088 [66, 67], and 25 as the cluster size (3750 total patients), this study will have at least 95% power to detect an absolute difference in imaging rates between professions of 6%. For patient factors, we hypothesise that increased pain severity and increased pain duration may be associated with inappropriate imaging [43], this study will have at least 90% power to detect a 10% difference in imaging rates with each 2-point increase in pain severity measured by the numerical rating scale (0 to 10), or each 2-week increased duration of low back pain.

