#### Clinician and patient recruitment

*Clinician participants (n = 175)* will comprise 50 each from chiropractic and physiotherapy, and 75 from family medicine. We are recruiting more family medicine clinicians than the other professions because lower numbers of patients with low back pain attend family medicine than chiropractic and physiotherapy. Our partner organisations will promote study participation via their normal communication strategies to their clinician members. We will invite clinicians in community-based practices chosen randomly from the lists of all registered clinicians in Ontario. From the College of Physicians and Surgeons of Ontario we will select only family doctors. From the College of Physiotherapists of Ontario we will select only physiotherapists whose primary work site is primary care. From the College of Chiropractors of Ontario we will use the full list.

We anticipate a 30% response rate based on our previous experience [51, 52], hence we will approach at least 600 clinicians to reach our sample size. To ensure the efficient use of project resources, we will target clinicians who practice in seven geographic regions within Ontario, Canada. These regions were selected to be representative of the mix of high and low population density areas, and different geographical regions: 1) Sudbury/North Bay; 2) Mississauga/Halton (Mississauga; Oakville; Milton); 3) Kitchener, Waterloo, and Guelph; 4) London, Ontario; 5) Central Toronto; 6) Southeast Ontario (Belleville; Brockville; Napanee; Smiths Falls; Kingston; Picton; Gananoque; Perth); 7) Ottawa region (Ottawa; Kanata; Nepean; Orleans).

We will invite clinicians to participate using a modified tailored design method [53] by sending a primer postcard, an invitation letter, two reminder letters and a telephone call. We will also use a snowball sampling technique, where, after clinicians are recruited, they will be asked to approach clinicians who work in the same practice, or other clinicians they know who they believe may be interested in participating.

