### Administrative data

Participating patients will be followed for 12 months using Ontario health administrative data held by the Ontario Institute for Clinical Evaluative Sciences (ICES) to determine if any imaging was undertaken (plain x-ray, CT scan, MRI, fluoroscopy, positron emission tomography (PET) scan, ultrasound). Although plain x-ray, CT scan and/or MRI are most likely to be ordered for patients with low back pain, we will capture all related imaging to be comprehensive in the assessment of inappropriate imaging. ICES data will also capture whether a pathological condition develops (defined with diagnoses at more than two healthcare visits), and surgery and emergency visits related to such a condition.

Some imaging may not be captured by the administrative data. Approximately 12% of chiropractors take their own plain x-rays and this information will not be captured in ICES data [58]; completed encounter forms by these chiropractors will indicate whether they took lumbar x-rays, and this information will also be collected via the patient-completed questionnaires. Also, some patients in Ontario elect to go to a private facility outside Ontario and individually pay for imaging. This information will be captured via the patient-completed questionnaires.

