### Quantitative data analyses

Characteristics of clinicians, patients and encounters will be summarised using descriptive statistics. We will calculate imaging rates per 100 low back pain patients with 95% confidence intervals and we will determine imaging rates for each primary care profession. We will undertake multilevel logistic regression analysis to determine the effects of clinician- and patient-level factors on inappropriate imaging. Clinician-level factors assessed will include age, sex, profession type, location of clinician training, clinician years in practice, ownership of imaging facilities, knowledge of imaging guidelines, and time spent with patient. Patient-level factors measured at baseline will include age, sex, race/ethnicity, insurance status, living in a metropolitan area, beliefs about usefulness of imaging, education level, duration/severity of low back pain, and three month measurement of satisfaction with treatment and adverse events. Patients consulting each clinician will form a cluster and will be considered as the second level in the multilevel logistic regression. We will also conduct a marginal logistic regression analysis to investigate the effects of clinician- and patient-level factors on inappropriate imaging and estimate the association between inappropriate imaging and explanatory factors in the marginal model using Generalised Estimating Equations. The analysis will allow examination of differences in results from the two models and determine whether the conclusions depend unduly on the model assumptions.

### Methods for study 2

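### The general claim of adequate power for clinician factors is not supported for ownership of imaging facilities, which may have only about six exposed clinicians

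*Protocol article*

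**What the plan says.** The Sample size justification opens with the general statement "The study will be adequately powered to determine factors associated with imaging behaviour, including both clinician (e.g. profession) and patient" characteristics. It then gives figures for three factors only: profession, pain severity and pain duration. For profession it claims "at least 95% power to detect an absolute difference in imaging rates between professions of 6" percentage points, "assuming base imaging rates across the professions range from 10 to 45" per cent. The inputs are "Using an intracluster correlation coefficient estimate of 0.088" and "25 as the cluster size (3750 total patients").

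Quantitative data analyses lists the clinician-level factors for the multilevel model. Alongside profession, age, sex and training location these are "clinician years in practice, ownership of imaging facilities, knowledge of imaging guidelines, and time spent with patient". Table 2 records ownership with one questionnaire item and does not restrict it to one profession. No power, effect size or expected prevalence is given for it.

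Two other places bear on how many owners to expect. Administrative data says "Approximately 12% of chiropractors take their own plain x-rays and this information will not be captured in ICES data". Clinician and patient recruitment says the clinicians "will comprise 50 each from chiropractic and physiotherapy, and 75 from family medicine".

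**The concern.** Power for a clinician-level yes/no factor depends mainly on how many clinicians fall in the smaller group. If ownership is rare, a total of 3750 patients does little to help, because the patients of one clinician are correlated and only a handful of clinicians carry the exposure. A sentence promising adequate power for clinician factors in general then credits the design with a property it lacks for this factor.

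Finding the factors associated with inappropriate imaging is a primary objective, and the results are meant to shape knowledge translation strategies. A non-significant ownership result from a study declared adequately powered invites the conclusion that ownership does not matter, when the data could not have distinguished no effect from a sizeable one.

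**Working it through.** **Inputs.** From the Sample size justification: ICC 0.088, cluster size 25, base rates 10% to 45%, and a 6-point difference (stated for professions). From Clinician and patient recruitment: 50 chiropractors, 50 physiotherapists, 75 family doctors. From Administrative data: about 12% of chiropractors take their own x-rays. Assumed, because not stated: two-sided 5% test; taking one's own x-rays stands for ownership; few owners in the other professions.

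**Design effect.** 1 + (25 − 1) × 0.088 = 3.112.

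**The plan's own figure first (professions, 6 points).** At 25 patients per clinician, 50 clinicians give 1250 patients (1250 / 3.112 = 402 effective) and 75 give 1875 (603 effective). Two-proportion normal approximation, pooled variance under the null:

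| Comparison | 10% v 16% | 27.5% v 33.5% | 39% v 45% |
|---|---|---|---|
| 1250 v 1250 | 72% | 46% | 41% |
| 1250 v 1875 | 79% | 52% | 47% |

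The unpooled form moves these by no more than 3 points. One-sided testing reaches at most 90% (1250 v 2500, 10% v 16%). Even with no design effect, 1250 v 1250 runs from 99% down to 86%. So at least 95% is not reproduced. At 1250 per profession, 95% power needs about 9 to 13 points.

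**Exposed clinicians.** 0.12 × 50 = 6 owners, leaving 44 non-owners among chiropractors. Patients: 6 × 25 = 150 (150 / 3.112 = 48 effective) and 44 × 25 = 1100 (353 effective). A binomial count with n = 50 and probability 0.12 falls between 3 and 10 about 92% of the time.

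**Power for ownership, within chiropractors, owners 6 points higher.** SE = √{3.112 × [p₁(1 − p₁)/150 + p₀(1 − p₀)/1100]}; power = Φ(0.06/SE − 1.96).

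| Owners v non-owners | SE | 0.06/SE | Power |
|---|---|---|---|
| 16% v 10% | 0.0552 | 1.088 | 19% |
| 33.5% v 27.5% | 0.0720 | 0.833 | 13% |
| 51% v 45% | 0.0767 | 0.782 | 12% |

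**Other standard variants.** A t reference on 48 degrees of freedom gives 12% to 19%. A pooled variance gives 12% to 27%. Comparing the 6 with all 169 other clinicians gives 13% to 20% unpooled and 13% to 31% pooled.

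**Larger effects.** With 6 v 44, a 10-point difference has 26% to 39% power. Eighty per cent power needs 18.9 points from a base of 10%, 21.3 from 27.5% and 20.6 from 45%.

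**If other professions also have owners.** Same formula, all 175 clinicians with 25 patients each, 6 points, over base rates from 10% to 45%:

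| Owners | Power |
|---|---|
| 12 | 35% down to 20% |
| 20 | 51% down to 30% |
| 40 | 76% down to 47% |

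**The case against.** The strongest reply is that no stated figure for ownership is wrong, because none is stated. The 6 points and 95% belong to the profession comparison. A reader might infer that the plan promises 95% power at 6 points for ownership; it does not. The 6-point yardstick is borrowed here only because the article gives no other for a clinician factor. What remains is the opening sentence, which does cover clinician factors generally.

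A reader might also infer that the plan expects exactly six owners. It does not say so. The 12% describes chiropractors who take their own x-rays and is there to explain a gap in the administrative data. Ownership is asked of all three professions, and snowball recruitment means a population share need not carry over. This stands: six is an assumption, and 12% to 19% is conditional on it. It does not rescue the general claim, because 12 to 20 owners still leave power at about 20% to 51%.

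A third tempting reading is that the GEE analysis will produce false positives for ownership. In an unadjusted simulation of 6 v 44 clinicians with no true effect, an uncorrected robust test with a 1.96 cut-off rejected about 11% to 12% of the time. But the article names no variance estimator or reference distribution, and such details are commonly left to an analysis plan. This is a reason for a safeguard, not an error in the document.

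Finally, nothing in the plan says that a non-significant factor will be reported as having no association. That is a risk of interpretation only.

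**Conclusion.** The concern holds as a point about an over-general power statement. If taking one's own x-rays stands for ownership and few other clinicians own facilities, about 6 clinicians are exposed. Power at 6 points is then about 12% to 19% (up to about 31% across standard variants), and only a difference of about 19 to 21 points is detectable with 80% power. These figures assume a two-sided 5% test, 25 patients per clinician and the plan's ICC. The exact percentages depend on the unknown number of owners; the conclusion that power is low at 6 points holds for up to at least 20 owners.

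Restricting the sentence to profession would not be enough, because the 95% figure for that comparison does not follow from the plan's ICC and cluster size either (about 41% to 79%, two-sided). The documents do not support the stronger readings that the plan sized ownership wrongly, fixed the number of owners at six, or specified a faulty GEE analysis.

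**What to change.** **Sample size justification.** Remove the general adequacy claim, or limit it to the factors actually sized: profession, pain severity and pain duration. Recompute the profession figure before keeping it. The figures for the two pain factors were not checked here. State the expected number of owners as an assumption, with the detectable difference that results (for about 6 owners, roughly 20 percentage points at 80% power), and update it once the baseline clinician questionnaires show the true count.

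**Quantitative data analyses.** Say that ownership will be reported as an estimate with its confidence interval, and that a non-significant result will not be read as no association.

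**Optional safeguard.** For clinician factors with few exposed clinicians, use small-sample-corrected robust standard errors in the GEE (for example Kauermann-Carroll or Mancl-DeRouen) with a t reference. In the simulation, a simple correction of this kind brought the false-positive rate to about 3% to 5% with 6 or 9 owners, though it was conservative (about 2% to 3%) with 4.

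**Cost.** Wording in two sections and, if the safeguard is adopted, a software option; no extra clinicians or patients. The price is a less favourable power statement and, with the correction, wider intervals for rare clinician factors.

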**Methods:**

The project will comprise an inception cohort study and a concurrent qualitative study. For the cohort study, we will recruit 175 primary care clinicians (50 each from physiotherapy and chiropractic; 75 from family medicine), and 3750 patients with a new episode of LBP who present to these clinicians. Clinicians will collect data in the clinic, and each participant will be tracked for 12 months using Ontario health administrative and self-reported data to measure diagnostic imaging use and other health outcomes. We will assess characteristics of the clinicians, patients and encounters to identify variables associated with inappropriate imaging. In the qualitative study we will conduct in-depth interviews with primary care clinicians and patients.

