Recruited clinicians will complete a baseline demographic questionnaire including: sex; age; training location; years in practice; and proximity of practice to imaging facility (see Additional file 1: Appendix 1 for questionnaire). Results of this questionnaire will be used to assess clinician representativeness by comparing to available province-wide clinician demographic characteristics and also be used as clinician-related factors when modeling inappropriate use of imaging.

*Patient participants (n = 3750):* Consecutive patients with low back pain will be invited to participate until up to 25 are recruited from each participating clinician. Research staff will visit each participating practice to train the practice staff and clinicians in the study procedures. To reduce possible selection bias, we will encourage practice staff at each location to follow a strategy suitable for their practice that maximises the chances of recruiting consecutive patients with low back pain. For clinicians in solo practice without reception staff, typical of some chiropractors and physiotherapists, clinicians will approach potential participants directly. For clinicians in circumstances where practice reception staff are likely to know in advance that a patient’s consultation is for low back pain, practice reception staff will be asked to inform every such patient about the study during the recruitment period and provide them with recruitment information to read in the waiting room. If the patient consents to participate, the practice staff will inform the clinician, who will then complete the enrolment process, including screening for participation.

We are allowing 12 months for patient recruitment; that is, approximately two patients with low back pain recruited per month per clinician, which is feasible based on incidence rates of low back pain presentations in these settings [4, 54, 55]. Practices will be offered reimbursement for staff time required to recruit patients and collect data.

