### Encounter data

After each patient consultation during the data collection period, participating clinicians will complete a handwritten 1-page encounter form (see Additional file 1: Appendix 3) for each of 25 consecutive consenting eligible patients with low back pain. There is one type of form for the initial encounter, and another, briefer form, for any follow-up consultations for the same low back pain episode. The encounter form is a modified form previously used in a chiropractic setting to systematically collect clinical data [51]; chiropractors reported that completing the form took 2–3 min per patient. The encounter forms for this project were piloted by two chiropractors, three physiotherapists and two family practitioners, who each recruited between two to five patients with low back pain over a six week period. Only minor changes were made to the form after the pilot study.

At the time of the patient’s initial consultation clinicians will record: key history and clinical findings; working diagnosis; diagnostic imaging ordered/taken; interventions provided or recommended; who is paying for the consultation; and, OHIP number for linkage purposes. Follow up encounter forms will be completed for each visit for up to 6 weeks to determine if any clinical indications for imaging arise. Six weeks was chosen because this is the time when people with low back pain are likely to be recovered, if pain is persisting they have progressed to the sub-acute stage, or if they have a pathological cause this is likely to be definitively diagnosed [57].

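### The stated power of at least 95% for a 6-point difference between professions does not follow from the plan's own ICC, cluster size and sample; recalculated power is about 41% to 72%

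*Protocol article*

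**What the plan says.** The Sample size justification compares inappropriate imaging rates among the three professions, "assuming base imaging rates across the professions range from 10 to 45" per cent. "Using an intracluster correlation coefficient estimate of 0.088" and "25 as the cluster size (3750 total patients" in total), it concludes that "this study will have at least 95% power to detect an absolute difference in imaging rates between professions of 6" per cent. It states no significance level, sidedness or number of patients per profession.

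The sample is described in three other places:

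- The abstract (Methods) says "we will recruit 175 primary care clinicians (50 each from physiotherapy and chiropractic; 75 from family medicine), and 3750 patients".
- Clinician and patient recruitment says the clinicians "will comprise 50 each from chiropractic and physiotherapy, and 75 from family medicine", and that consecutive patients are invited "until up to 25 are recruited from each participating clinician".
- Encounter data has clinicians complete a form "for each of 25 consecutive consenting eligible patients with low back pain".

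Quantitative data analyses treats the patients of one clinician as a cluster, so the ICC applies to the planned comparison.

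**The concern.** An ICC of 0.088 with 25 patients per clinician makes the variance about three times that of independent patients. A 6-point difference is small for roughly 400 effective patients per group, particularly towards a rate of 45%, where the binomial variance is near its maximum. A claim of at least 95% over the whole 10 to 45% range therefore looked too high.

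The difference between professions is the first power figure in the section. Profession is a named factor under the first primary objective, and differences between clinician types in recommending imaging are secondary objective 3. If the power is overstated, a non-significant comparison will be taken as strong evidence that professions do not differ by 6 points, and strategies targeted at each profession could be shaped by that reading.

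The inputs also do not fit together exactly: 175 clinicians at 25 patients each is 4375, and 3750 patients at 25 each is 150 clinicians.

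**Working it through.** **Inputs from the protocol.** ICC 0.088; cluster size 25; 3750 patients; base rates 10 to 45%; difference 6 points (all from Sample size justification); 50, 50 and 75 clinicians (Clinician and patient recruitment).

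**Assumptions.** Two-sided alpha 0.05; 1250 patients per profession; pairwise comparison; ICC on the proportion scale. The article states none of these, so each is varied below except the ICC scale, which is taken up with the objections.

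**Step 1: effective sample size.**

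- Design effect = 1 + (m − 1) × ICC = 1 + 24 × 0.088 = 3.112
- Effective patients per profession = 1250 / 3.112 = 401.7

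**Step 2: attempt to reproduce the stated 95%.**

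Power = Φ(0.06 / √[(p₁q₁ + p₂q₂) / 401.7] − 1.96)

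| Rates | p₁q₁ + p₂q₂ | Standard error | 0.06 / SE | Power |
|---|---|---|---|---|
| 10 v 16% | 0.2244 | 0.0236 | 2.538 | 72% |
| 20 v 26% | 0.3524 | 0.0296 | 2.026 | 53% |
| 30 v 36% | 0.4404 | 0.0331 | 1.812 | 44% |
| 39 v 45% | 0.4854 | 0.0348 | 1.726 | 41% |

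The stated figure is not reproduced at any pair in the range. A pooled-variance formula gives 71.6%, 52.4%, 44.0% and 40.6%.

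**Step 3: vary the assumptions.** The second column is the easiest pair inside the stated range, the third the hardest. Where two values appear, they depend on which group has the lower rate.

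| Variant | 10 v 16% | 39 v 45% |
|---|---|---|
| One-sided 5% | 81% | 53% |
| Bonferroni for three pairs (0.05/3) | 56% | 25% |
| Average cluster of 21.4 (3750/175), 1250 v 1250 | 76% | 44% |
| 75 family doctors at 16.7 patients (design effect 2.38) v 1250 at 25 | 76 to 78% | 45% |
| 75 family doctors at 25 (1875 patients) v 1250 | 78 to 81% | 47% |
| One profession v the other two pooled (1250 v 2500) | 81 to 86% | 51 to 52% |
| 1875 v 1875 | 87% | 56% |
| 4375 patients, family medicine v the other two pooled (1875 v 2500) | 91 to 92% | 62% |
| No design effect, 1250 v 1250 | 99% | 86% |

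Every variant that keeps the ICC as a proportion-scale design effect stays below 95%, even at the easiest pair. Ignoring clustering exceeds 95% at 10 v 16% but fails at the top of the range. At 10 v 16% with 1250 per profession, 95% power requires an ICC of about 0.022, a quarter of the stated value.

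**Step 4: what the design can detect.** Solving the Step 2 formula for the difference, with 1250 per profession and the base rate as the lower of the two:

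| Base rate | 80% power | 95% power |
|---|---|---|
| 10% | 6.7 points | 8.9 points |
| 20% | 8.4 points | 11.0 points |
| 30% | 9.4 points | 12.1 points |
| 45% | 9.8 points | 12.6 points |

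Conversely, 95% power for 6 points would take about 814 × 3.112 = 2533 patients per profession at 10 v 16%, and about 1756 × 3.112 = 5465 at 39 v 45%.

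**Step 5: the sample.** 175 × 25 = 4375; 3750 / 25 = 150; 3750 / 175 = 21.4. If chiropractors and physiotherapists each fill 25, they supply 2 × 50 × 25 = 2500 patients, leaving 1250 / 75 = 16.7 per family doctor.

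**The case against.** Four points can be made for the plan.

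- **Unstated assumptions.** The 41% to 72% range rests on an alpha, sidedness and allocation that the article does not give. This is fair, and the range should be read with those conditions attached. Changing them moves the numbers but does not restore the claim, as Step 3 shows.
- **ICC scale.** The analysis is multilevel logistic regression, so 0.088 could be a latent-scale value. The proportion-scale ICC would then be about 0.03 to 0.04 at rates of 10 to 16%. Power for 10 v 16% becomes 90% at 1250 per group, and passes 95% if family medicine has 1875 patients and the higher rate (96%), or with one profession against the other two pooled (95 to 98%). This is the best route to the stated figure, but it works only at the bottom of the range: at 39 v 45% the same layouts give 47 to 59%.
- **Omnibus test.** Rates rising in 6-point steps over three professions (10/16/22%) give 99% power on a 2-df test. That is a 12-point spread, not a 6-point difference, and it falls to 87% at 39/45/51%. If one profession alone differs by 6 points, the omnibus test has 41 to 78%.
- **3750 against 4375.** The recruitment section makes 25 a ceiling and expects fewer low back pain patients in family medicine, so 3750 is a plausible total. What stands is narrower: the power calculation then uses a uniform cluster size of 25 that does not hold in family medicine.

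It is also true that the plan reports imaging rates with 95% confidence intervals, which would limit misreading of a null result for a careful reader. That does not make the printed power figure correct.

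**Conclusion.** The concern holds. With the stated ICC, cluster size and total, power for a 6-point difference between professions is about 72% at 10 v 16%, falling to 41% at 39 v 45%, against a stated minimum of 95%. Those values assume two-sided 5%, 1250 patients per profession and a proportion-scale ICC. The conclusion that 95% does not hold across 10 to 45% depends on none of these. The most favourable readings reach 95% only at the lowest rates, or by testing a spread wider than 6 points, and 39 v 45% falls short even with clustering ignored.

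The mismatch between 25 per clinician and 3750 patients is secondary and partly explained by the recruitment text. How the sponsor obtained 95% cannot be told from the article. The separate 90% power statement for patient factors was not checked.

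**What to change.** Replace the power statement for professions with the figure the design delivers. For example: at two-sided 5% and with 1250 patients per profession, pairwise comparisons between professions have 80% power for differences of about 7 to 10 percentage points, and 95% power for about 9 to 13 points, for base rates of 10 to 45%.

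Alongside it:

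- State alpha and sidedness, the scale of the ICC, and whether the three pairwise comparisons are adjusted for multiplicity. If they are, the detectable differences must be recalculated, because power for 6 points drops to about 25 to 56% under Bonferroni.
- Give patients and average cluster size by profession and base the calculation on them: 50 × 25, 50 × 25 and 75 × 16.7 (1250 each, 3750 in all), or restate the total as 4375. Align the encounter form text with the ceiling of 25 in the recruitment section.
- If other assumptions produced 95%, set them out so that the figure can be reproduced.

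The cost is a recalculation and some rewording. The stated power becomes less favourable; the design, data collection and analysis do not change, and no extra patients are needed.
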